## Abstract

Controlled ovarian hyperstimulation (COH) is essential for the success of in vitro fertilization (IVF). Evidence showing the comparison of different COH protocols remains predominantly of low certainty and derives from unspecified infertile and highly heterogeneous populations. Thus, personalized approaches to examine the response of patients to the various COH protocols need to be investigated. Data from in vitro and animal studies have identified the mechanistic target of rapamycin (mTOR) and Hippo signaling pathways play a key role in follicular homeostasis and oocyte quality. To be specific, current data indicate the controlled activation of mTOR and the controlled inhibition of the Hippo pathway within the ovarian granulosa cells (GC). Both are reported to lead to a nurturing follicular microenvironment, increase oocyte quality, and potentially improve reproductive outcomes. As intracellular markers, phosphorylated/unphosphorylated levels of the pathways’ main downstream mediators could be included among the candidate “personalized” predictors of patients’ response to COH protocols and final IVF outcomes. Based on these hypotheses, we make a preliminary attempt to investigate their validity: We propose a prospective cohort study to compare the levels of certain phosphorylated/unphosphorylated components of the investigated pathways (mTOR, ribosomal protein S6 kinase beta-1 (p70S6K-1), yes-associated protein-1 (YAP-1), and transcriptional coactivator with PDZ-binding motif (TAZ)) within the follicular fluid-isolated GC between women undergoing gonadotropin-releasing hormone (GnRH) antagonist/“short” protocols and those receiving GnRH agonist/“long 21” protocols. A case-control design comparing these levels between women achieving pregnancy and those who did not is further planned. Additional analyses addressing the population’s expected heterogeneity are planned after the completion of the pilot phase, during which 100 participants undergoing IVF are intended to be recruited. At this stage, these hypotheses are solely based on in vitro/animal data, and thus, similar studies on humans in this respect are necessary for the investigation of their potential validity.

## 1. Introduction

### 1.1. Controlled Ovarian Hyperstimulation (COH) Protocols

Controlled ovarian hyperstimulation (COH) is a determining stage for the success of in vitro fertilization (IVF) as it leads to the necessary pooling of oocytes available for retrieval and subsequent creation of embryos for intrauterine transfer [1]. COH may be divided into three distinguishable phases: firstly, stimulation of multi-follicular development (for which the following have been used: human menopausal gonadotrophin (hMG), a purified (p-FSH) or highly purified follicle stimulating hormone (hp-FSH), a urinary product with follicle-stimulating hormone (u-FSH) and luteinizing hormone (LH) activity, and various recombinant FSH (rFSH) and LH (rFSH/rLH)); secondly, pituitary suppression towards the prevention of the LH surge and premature ovulation through the administration of gonadotropin-releasing hormone (GnRH) agonists or antagonists; and finally, the triggering of oocyte maturation and ovulation by using human chorionic gonadotropin (hCG) or GnRH agonists [2].

There is a continuing attempt to compare the efficacy and safety of the various COH protocols [2,3]. Their implementation, based on the administration of agonists of gonadotropin-releasing hormone (GnRH) (“long”), likely leads to comparable live birth rates (LBR) to those based on the GnRH antagonists (“short”). The latter reduces the probability of ovarian hyperstimulation syndrome (OHSS) in predicted normal or high responders [4,5,6]. The use of rFSH in COH in normal responders undergoing the “long” GnRH agonist protocols may also lead to lower fresh-cycle LBR compared to that of when hMG is used [5]. However, there are certain noteworthy limitations of the existing very low- to low-certainty evidence. Such include the lack of high-quality trials, the inclusion of unspecified populations of infertile couples in the vast majority of trials, and the insufficiency of data to allow separate estimations for poor and high responders or comparison of all possible combinations of GnRH agonists/antagonists with the gonadotrophin preparations and triggering agents [4,5]. The significant inconsistency between studied populations and interventions applies to most of the literature on assisted reproductive techniques (ART). Furthermore, it has been identified as one of the main research-related factors responsible for the plateauing of ART success rates [7,8]. Further potential reasons include flaws in the design, execution, and/or reporting of the current studies, as well as factors linked with issues related to clinical practice, such as the lack of the true efficacy of “add-on” treatments and the “industrialization” of IVF [7,8,9]. It therefore seems that the exploration and the proper use of markers that could provide clinicians with a more individualized picture of a patient’s probability of an adequate response to a specific COH protocol are, nowadays, crucial [10,11,12,13].

It could also be hypothesized that different categories of infertile patients undergoing IVF may respond differently to specific COH protocols, and consequently, this may lead to different outcomes [12]. The administered regimens affect the hormonal profile of each woman in a unique way, which is linked with her characteristics, such as demographic parameters or her personal unique history (e.g., different types of infertility such as ovulatory or tubal disorders, or endometriosis). In this respect, there is a need to investigate the intracellular pathways that may better reflect the effects of COH in combination with the individual profile of each patient separately. Two such pathways in ovarian granulosa cells (GC) that play an important role in follicular development are the phosphatidylinositide triphosphate kinase (PI3K)/Ak strain transforming (Akt) protein kinase/mechanistic target of rapamycin (mTOR) and Hippo/yes-associated protein-1 (YAP-1)—transcriptional coactivator with PDZ-binding motif (TAZ) [14].

### 1.2. The mTOR-Related Pathways in Ovarian GC

mTOR is a serine-threonine kinase that acts as the active catalytic subunit of two intracellular complexes, namely, the mTOR complex 1 and mTOR complex 2. A plethora of studies have demonstrated that mTOR may be activated by multiple signaling pathways within the ovarian GCs, including the PI3K/Akt and the cyclic adenosine monophosphate (cAMP)/cAMP-dependent protein kinase A (PKA)/mitogen-activated protein kinase (MAPK)/extracellular signal-regulated kinases (ERK) [14,15,16,17,18,19]. These exhibit dynamic interactions with one another and can be activated by various factors, including the FSH, the epidermal growth factor (EGF), the vascular epithelial growth factor (VEGF), and the insulin or insulin growth factor-1 (IGF-I) [14,16,19,20,21]. Ribosomal protein S6 kinase beta-1 (p70S6K-1) and eukaryotic translation initiation factor 4E (eIF4E) are the main downstream effectors of the mTOR pathway [15,22,23].

Accumulating evidence from in vitro studies or animal models has demonstrated that the stimulation of mTOR and its downstream effectors in ovarian GCs may orchestrate the processes of quiescence, activation, and survival of primordial follicles; induce proliferation and differentiation of GCs and meiotic maturation of oocytes [24,25,26]; and suppress the phenomena of autophagy and apoptosis [27,28,29,30]. The activation of mTOR via the described pathways seems to be an essential mediator for the bidirectional communication between GCs and oocytes. These interactions lead to a nurturing microenvironment for follicular growth, which in turn empowers the oocyte’s developmental potential [31,32,33,34]. A better oocyte developmental competence is associated with an increased ability of the oocyte to complete meiosis and, subsequently, undergo fertilization, implantation, embryogenesis, and term development [31,33]. In contrast, the overactivation of mTOR-related pathways in in vitro or animal studies has been associated with ovarian aging and the pathogenesis of premature ovarian insufficiency due to massive maturation of primordial follicles [35,36], polycystic ovary syndrome (PCOS) [37,38], endometriosis [39], and ovarian cancers [40,41,42]. In the same context, its inhibition may lead to an increase in ovarian reserve and lifespan [43,44] and the mitigation of OHSS symptom severity [45].

### 1.3. The Hippo Pathway in Ovarian GC

The Hippo pathway is mediated by the phosphorylation of the mammalian sterile 20-related kinases 1 and 2 (Mst1/2), which activate the large tumor suppressor kinases 1 and 2 (Lats1/2). The latter, phosphorylate the translation activators YAP-1 and TAZ, which thus remain outside the nucleus and are degraded in the cytoplasm [46,47,48]. Hippo is inhibited during ovarian stimulation through cytoskeletal reorganization, extracellular matrix stiffness, ovarian fragmentation, and the activation of G protein-coupled receptors, integrins, or growth factors [46,49]. Thus, the unphosphorylated YAP-1 and TAZ activators freely enter the nucleus, form complexes with TEA domain family member transcription factors (TEADs), and further stimulate the transcription of proliferation-related and growth factor genes [47,48,50].

Like the mTOR-related pathways, the Hippo pathway plays a key role in the control of follicular growth and homeostasis. The Hippo pathway is reported to regulate the balance between GC proliferation (which dominates before ovulation when Hippo is predominantly inactive), steroidogenesis, and differentiation of the cells into a luteal phase (processes that dominate after ovulation when Hippo is active) [14,47]. The Hippo pathway effectors interact with the EGF-like signaling [51], as well as the components of the aforementioned intracellular signaling involving mTOR [12,14,52]. Excessive inhibition of the Hippo pathway and unrestrained inflow of the chief final mediators YAP-1 and TAZ into the nucleus have been involved in the development of PCOS [46,53], endometriosis [54,55], and ovarian tumorigenesis [56]. On the other hand, in vitro fragmentation and controlled inhibition of Hippo (combined with administration of PI3K/Akt/mTOR activators) can promote the growth of preantral follicles in patients with primary ovarian insufficiency [57,58,59]. According to a recent randomized controlled trial, the fragmentation of one ovary for follicular activation compared to no intervention in women with poor ovarian response resulted in an increase of the antral follicle count (AFC), an 18.8% reduction in the phosphorylated YAP-1/unphosphorylated YAP ratio (indicating Hippo pathway inhibition), but this had no impact on the IVF outcomes [60].

Taking all the above into consideration, the controlled activation (i.e., phosphorylation) of mTOR and its related downstream effectors (e.g., p70S6K-1) and controlled inhibition of Hippo (i.e., reduction of phosphorylated YAP-1, TAZ) are of potential benefit for the ovarian GC-oocyte interactions, oocyte quality, and reproductive outcomes. This hypothesis remains to be reinforced or disproved in humans.

## 2. Objectives

In this paper, we aim to express the hypothesis that the activity of both the mTOR (the mechanistic target of rapamycin) and Hippo pathways within the GCs isolated by the follicular fluid of women undergoing IVF may be affected by the type of protocol used for COH; these differences in activity may also influence the outcomes of the IVF cycle. As discussed above, these pathways orchestrate the processes of proliferation, differentiation, and apoptosis of GCs. Such processes are directly related to the development and maturation of the follicles, the quality of the oocytes, and potentially, the outcomes of the IVF cycle. Data to form this hypothesis currently derive from in vitro/animal studies; thus, this study design involving humans is original in the literature.

To initially test the potential validity of this hypothesis, we propose the measurement of the activity of the two pathways through the levels of the phosphorylated/unphosphorylated forms of specific proteins: i. mTOR, p70S6K-1 to reflect the downstream activation of mTOR-related pathways and ii. YAP-1, TAZ to reflect the activation of Hippo. The phosphorylated forms of mTOR and p70S6K-1 represent the increased activation of the mTOR-related signaling pathways, whereas the decreased phosphorylated and elevated unphosphorylated levels of YAP-1 and TAZ signify the Hippo inhibition, and therefore intensified the signals for GC proliferation. Levels of these forms will be compared between GCs isolated from the follicular fluids of women receiving GnRH agonists and those receiving GnRH antagonists for pituitary suppression. This first stage of the study will be conducted prospectively.

We further aim to compare these measurements between women achieving positive IVF outcomes and those who did not. In this way, we will attempt to examine whether the potential differences in the activity of the two pathways could be correlated with the final (primary and/or secondary) outcomes of the IVF cycle. This second stage will be conducted through a case-control design. The study is aimed to be divided into an initial pilot phase, during which the feasibility of the design will be assessed, and a final phase, during which a growing registry is to be created where additional subgroup analyses (addressing the inconsistency of the population) are to be conducted.

The upper goal of this research effort is to investigate whether measuring the activity of these intracellular pathways can somehow predict the ovarian response to COH protocols and/or final IVF outcomes by reflecting a more personalized state of the microenvironment of the ovarian GCs. The need for immediate study and further knowledge of these paths arises from the growing expectations of infertile couples to increase the chance of successful outcomes at the lowest possible financial cost while minimizing clinical procedures (reduction of the number of IVF attempts) and/or the probability of unwanted outcomes (e.g., miscarriage, ectopic pregnancy, and OHSS).

## 3. Materials and Methods

### 3.1. Study Design

Comparison of the phosphorylated/unphosphorylated levels of the pathways’ components following the administration of GnRH antagonist/“short” protocols versus GnRH agonist/“long 21” protocols will be conducted through a prospective-cohort design. A comparison of levels between women achieving certain predefined outcomes within the IVF cycle and those not reaching these outcomes will be carried out through a case-control design. The pilot phase of the study, during which 100 women undergoing IVF are planned to be recruited, will be conducted in the Second Department of Obstetrics and Gynecology of “Aretaieion Hospital”, Athens, Greece, a tertiary academic center within a university IVF unit (Figure 1). Institutional review board approval will be received, and informed consent will be obtained from all participants. Following the potential success of the pilot phase, more public/private study centers are to be added towards the increased recruitment of the study subjects.

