### 3.4. Intended Comparisons and Outcomes

The phosphorylated/unphosphorylated levels of the four downstream effectors of the investigated pathways within the isolated GCs will be compared between women receiving a GnRH agonist protocol and those being administered a GnRH antagonist protocol. Furthermore, a comparison of the activity of these two pathways will be made concerning certain desired or unwanted outcomes of the IVF cycle, during which the pathways’ measurements took place. Live birth after the cycle of measurements will serve as the primary outcome of the case-control study. Clinical pregnancy (defined as the presence of a gestational sac on ultrasound scan at 6–7 weeks of gestation), implantation rate (defined as the number of sacs detected divided by the number of embryo transfers), ongoing pregnancy (i.e., presence of a positive fetal heartbeat on ultrasound from a gestational age of 10 weeks onwards), miscarriage (i.e., loss of pregnancy before 22 completed weeks of gestational age), ectopic pregnancy, and OHSS will be the secondary outcomes of the study.

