### 3.5. Data Analysis

Categorical variables will be presented as frequencies and percentages, whereas numerical variables will be presented as mean (standard deviation) or median (interquartile range) based on the normality of the data. A normality check will be performed by using the Shapiro–Wilk test. Independent samples *t*-test or Mann–Whitney U test (as per normality or not of data) will be utilized for comparisons regarding numerical variables, whereas chi-square or Fisher’s exact (if applicable) tests will be used for categorical variables. Following the pilot phase (during which the following analyses would be underpowered), further analyses are being planned. Comparisons of the pathways’ activity will be made by patients’ age (<35 vs. >35 years of age), by category of infertility (male, female, or unexplained), and by the female infertility-related factor (e.g., PCOS and endometriosis). Concerning the IVF outcomes, multivariable logistic regression models are further being planned.

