## Figures and Tables

**Figure 1 jcm-11-06131-f001:**
[figure not shown]
Illustration of the prospective and case-control phases of the planned study. Eligible participants will be women aged 30–40 undergoing stimulated IVF cycle (i.e., not undergoing natural or mild IVF protocols) due to infertility of male, female factor, or unexplained etiology. The number of participants (100) refers to the targeted sample of the pilot phase. Following the successful completion of this phase, more study centers and subjects are intended to be included. (**a**) Prospective phase of the designed study. Levels of certain phosphorylated components of the investigated mTOR and Hippo pathways will be compared between women receiving GnRH agonist/“long 21”protocols and those receiving GnRH antagonist/”short” protocols. These levels will be measured via special ELISA kits by using follicular fluid-isolated ovarian GCs from each group. (**b**) Case-control phase of the planned study. Already measured levels of certain phosphorylated components of the investigated mTOR and Hippo pathways will be retrospectively compared between women achieving predefined (positive/negative) IVF endpoints and those not. Both schemes were created with Biorender.com (www.biorender.com, 19 September 2022). A license for the use of BioRender icons appearing in both schemes and the publication has been granted. Both schemes are original and were created by the authors. ***Abbreviations:*** GnRH, gonadotropin-releasing hormone; BMI, body mass index; AMH, anti-Mullerian hormone; FSH, follicle stimulating hormone; LH, luteinizing hormone; PRL, prolactin; AFC, antral follicle count; E2, estradiol; PG, progesterone; no, number; FF, follicular fluid; GC, granulosa cell; RLB, red blood cell lysing buffer; ELISA, enzyme-linked immunosorbent assay; mTOR, the mechanistic target of rapamycin; p70S6K-1, ribosomal protein S6 kinase beta-1; YAP-1, yes-associated protein-1; TAZ, transcriptional coactivator with PDZ-binding motif; OHSS, ovarian hyperstimulation syndrome.

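### Miscarriage and ectopic pregnancy are compared with all women without the event, including women who never conceived, which pushes a pregnancy-favouring marker towards an apparent association with loss

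*Protocol article*

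**What the plan says.** Section 3.1 sets up the second stage of the study by splitting the cohort on outcome: "women achieving certain predefined outcomes within the IVF cycle and those not reaching these outcomes will be carried out through a case-control design". The Figure 1 legend, part (b), is more explicit: the levels already measured "will be retrospectively compared between women achieving predefined (positive/negative) IVF endpoints and those not". Section 4 repeats the same split for desired and unwanted outcomes alike.

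Section 3.4 says that pathway activity will be compared "concerning certain desired or unwanted outcomes of the IVF cycle". Live birth is the primary outcome of this stage. After the pregnancy endpoints, the list of secondary outcomes ends: "miscarriage (i.e., loss of pregnancy before 22 completed weeks of gestational age), ectopic pregnancy, and OHSS will be the secondary outcomes of the study". No at-risk group is attached to miscarriage or ectopic pregnancy.

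The pool that supplies both groups is the pilot cohort, for which "100 women undergoing IVF are planned to be recruited" (section 3.1). Enrolment does not depend on conception. In section 3.5, an independent-samples t-test or Mann–Whitney test "will be utilized for comparisons regarding numerical variables", without adjustment. Multivariable logistic models for the IVF outcomes are planned only after the pilot.

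**The concern.** Only a pregnant woman can miscarry or have an ectopic pregnancy. If the comparator is every woman without the event, it pools women whose pregnancy went well with women whose cycle failed. All cases conceived, while part of the comparator did not. The contrast therefore carries the pregnant-versus-not-pregnant difference in the marker as well as any difference related to loss.

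The protocol's own hypothesis makes this matter. Section 1.3 ends by proposing that mTOR activation and Hippo inhibition "are of potential benefit for the ovarian GC-oocyte interactions, oocyte quality, and reproductive outcomes". If that is right for conception, women who miscarry will tend to have a more favourable marker than a comparator diluted by failed cycles. A favourable marker then looks associated with loss. If the marker also lowers the risk of loss, the two forces pull in opposite directions and the protective effect can vanish from the result. Section 2 names miscarriage and ectopic pregnancy among the unwanted outcomes that the research hopes to make less likely, so a misleading answer on them defeats part of the purpose.

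**Working it through.** **Stated figure.** The only figure given is the pilot target of 100 women. It comes with no power calculation, so there is nothing to reproduce.

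**Inputs.** From the documents: N = 100, the comparator rule, and the unadjusted two-group tests. Assumed, because the documents give no values: pregnancy rate p (20–60%), loss rate among pregnancies m (10–30%), and marker gap d between pregnant and non-pregnant women (0.5 SD).

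**Step 1: who is in the comparator.** Cases = N·p·m. Comparators = N(1 − p·m), of whom N(1 − p) never conceived. The never-pregnant share is (1 − p)/(1 − p·m).

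At p = 35% and m = 20%: 35 pregnant, 7 losses, 93 comparators, 65 never pregnant; 65/93 = 0.699.

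**Step 2: spurious difference when the marker is unrelated to loss.** Cases sit at the pregnant mean. The comparator sits below it by d times the never-pregnant share. The artefact is d(1 − p)/(1 − p·m).

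At p = 35% and m = 20%: 0.5 × 65/93 = 0.35 SD.

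| p | Never-pregnant share (m = 10% to 30%) | Artefact at d = 0.5 SD |
|---|---|---|
| 20% | 0.82–0.85 | 0.41–0.43 |
| 30% | 0.72–0.77 | 0.36–0.38 |
| 40% | 0.63–0.68 | 0.31–0.34 |
| 50% | 0.53–0.59 | 0.26–0.29 |
| 60% | 0.43–0.49 | 0.21–0.24 |

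The never-pregnant form a majority when p < 0.5/(1 − m/2), that is below 0.53, 0.56 or 0.59 for m = 10%, 20% or 30%. The bias needs no majority.

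The same formula applies to ectopic pregnancy, with m as the ectopic share. As m becomes small, the never-pregnant share tends to 1 − p; at p = 35% the artefact tends to 0.5 × 0.65 = 0.33 SD.

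**Step 3: simulation.** In 2,000,000 women with about 36% pregnant, a pregnancy odds ratio of 1.65 per SD of marker, 20% loss and no effect of the marker on loss, losses differ from all other women by +0.33 SD. They differ from pregnant women without loss by 0.00 SD.

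**Step 4: what happens if the marker does protect against loss.** Same pregnancy odds ratio of 1.65:

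| True loss odds ratio per SD | Versus all other women | Versus pregnant, no loss |
|---|---|---|
| 0.8 | +0.15 SD | −0.20 SD |
| 0.7 | +0.04 SD | −0.34 SD |
| 0.6 | −0.08 SD | −0.47 SD |

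At 0.8 the sign is reversed, at 0.7 the effect is hidden, and at 0.6 it is much attenuated. With a weaker pregnancy odds ratio of 1.3, the all-women contrast is about zero at a loss odds ratio of 0.8, where the within-pregnant difference is −0.21 SD.

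**Step 5: visibility in the pilot.** Over the Step 2 ranges there are 2 to 18 losses. The chance that the artefact reaches two-sided 0.05 is about 7–20%.

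**The case against.** The best defence is that the sentence in section 3.1 is a generic description of the design. Its verbs suit desired endpoints, and section 2 words the aim around positive outcomes. Section 3.4 sets no comparator, and its definition of miscarriage presupposes a pregnancy. Per-endpoint denominators are the kind of detail that an article leaves to a fuller document. That would carry weight if section 3.1 stood alone. It does not dispose of the Figure 1 legend, which names negative endpoints and sets the remaining women against them, or of section 4, which repeats the rule. The text states a rule, and for two endpoints that rule is unsuitable.

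Other parts of the defence stand:

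- A reader might infer that most comparators were never pregnant. No document figure supports this. It depends on an assumed pregnancy rate below about 53–59% and fails at 60%.
- A reader might infer that a beneficial marker will be reported as causing loss. Step 4 shows that the direction is not assured, and section 2 speaks of correlation and prediction, not cause. The marker can appear associated with loss, or a protective effect can be masked.
- The pilot would rarely show the artefact as significant, and it is meant to assess feasibility. However, bias does not fall with sample size, and the plan foresees more centres and a growing registry. Logistic regression on the same denominator would not, by itself, remove the never-pregnant women.
- Restricting to women who conceived has its own price. The marker is measured at retrieval, and conception is a later event that it may influence. If unmeasured factors affect both conception and loss, the restriction can introduce selection bias.

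**Conclusion.** The point holds for two secondary outcomes, miscarriage and ectopic pregnancy. As written, their comparator includes women who could not have had the event. With a marker gap of 0.5 SD and no effect on loss, the spurious difference is about 0.21–0.43 SD over the assumed rates, and 0.35 SD at 35% pregnancy and 20% loss. All these rates and the gap are assumptions; the size scales directly with the gap. The direction of the bias follows from the protocol's own hypothesis, but the net result also depends on any true effect on loss.

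The primary outcome, live birth, is not affected, and neither are clinical pregnancy and ongoing pregnancy. OHSS is not affected either, since every stimulated woman is at risk. This should be corrected before the comparisons are run, but it does not undermine the study as a whole.

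**What to change.** State the at-risk set in section 3.4 and match the Figure 1 legend to it:

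- Miscarriage: compare with pregnancies that did not end in miscarriage, confirmed on the same basis as the cases. Section 3.4 counts any pregnancy loss before 22 weeks, whereas clinical pregnancy requires a sac on ultrasound at 6–7 weeks. If earlier losses count as cases, the comparators must be counted from the same starting point.
- Ectopic pregnancy: compare with confirmed pregnancies that were not ectopic.
- Live birth, clinical pregnancy, ongoing pregnancy and OHSS: as planned.

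Carry the same denominators into the later logistic models. Note conditioning on conception as a limitation. The all-women contrast may be kept as a descriptive supplement, labelled as such.

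**Cost.** About one sentence and no new data, since section 3.2 already has the cycle outcomes recorded. Precision falls a little: at 35% pregnancy and 20% loss, the miscarriage comparator drops from 93 to 35 − 7 = 28. The difference detectable with 80% power at two-sided 0.05 moves from about 1.11 SD (7 versus 93) to about 1.22 SD (7 versus 28). The small number of cases drives both figures, so little is lost by restricting.
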